## Abstract

**Introduction:**

Simulation-based studies indicate that crisis checklist use improves management of patients with critical conditions in the emergency department (ED). An interview-based study suggests that use of an emergency manual (EM)—a collection of crisis checklists—improves management of clinical perioperative crises. There is a need for in-depth prospective studies of EM use during clinical practice, evaluating when and how EMs are used and impact on patient management.

**Methods and analysis:**

This 6-month long study prospectively evaluates a digital EM during management of priority 1 patients in the Skåne University Hospital at Lund’s ED. Resuscitation teams are encouraged to use the EM after a management plan has been derived (‘Do-Confirm’). The documenting nurse activates and reads from the EM, and checklists are displayed on a large screen visible to all team members. Whether the EM is activated, and which sections are displayed, are automatically recorded. Interventions performed thanks to Do-Confirm EM use are registered by the nurse. Fifty cases featuring such interventions are reviewed by specialists in emergency medicine blinded to whether the interventions were performed prior to or after EM use. All interventions are graded as indicated, of neutral relevance or not indicated. The primary outcome measures are the proportions of interventions performed thanks to Do-Confirm EM use graded as indicated, of neutral relevance, and not indicated. A secondary outcome measure is the team’s subjective evaluation of the EM’s value on a Likert scale of 1–6. Team members can report events related to EM use, and information from these events is extracted through structured interviews.

**Ethics and dissemination:**

The study is approved by the Swedish Ethical Review Authority (Dnr 2022-01896-01). Results will be published in a peer-reviewed journal and abstracts submitted to national and international conferences to disseminate our findings.

**Trial registration number:**

NCT05649891.

STRENGTHS AND LIMITATIONS OF THIS STUDYTo date, the majority of studies of emergency manuals (EMs)—collections of crisis checklists— have been simulation-based, with the notable exceptions of one interview-based and one prospective study. This study prospectively evaluates an EM during the management of unselected, consecutive priority 1 patients in an emergency department over a 6-month period.Some of the data on patient characteristics and EM use are automatically registered, while other EM use data are actively registered by the documenting nurse.The study aims to determine whether interventions carried out thanks to checklist use are indicated, of neutral relevance or not indicated based on the clinical context, as assessed by external reviewers.The external review process is based on information available from patient records, which may not convey all the relevant factors affecting clinical decisions.The study is not a randomised controlled trial and is not powered nor designed to detect causal relationship between EM use and patient outcome.

## Introduction

### Checklists

A checklist is a cognitive aid—consisting of a list of assessments or actions—designed to be carried out systematically. The function of checklists is to improve task performance; checklists are essentially knowledge-translation tools that promote completeness, consistency and alignment with best practice guidelines when carrying out a task.^1^ Checklists work by directing focus, providing facts^2^ and guiding—though not dictating—decision-making. Checklists are also believed to improve performance through other mechanisms, such as reducing mental workload, promoting a shared mental model among team members and empowering team members to voice concerns.^3–5^

There are two basic modes of checklist use.^6^ In Read-Do mode, checklists are used as the task is performed to guide task completion. During the Do-Confirm mode, checklists are used after task performance to verify completeness. Cognitive aids may even be used to retrieve specific information (for instance, the dosage of a specific medication in a specific setting), so-called Sampling mode.^6 7^ Checklists may be used by one or several people, silently or read aloud,^6^ and can be categorised according to the circumstances in which they are used: normal (or routine) situations, emergency situations, and atypical (or non-normal) situations.^6 8^

### Checklists for routine situations in healthcare

The WHO Surgical Safety Checklist^9^ and the Surgical Safety Patient System^10^ are examples of checklists used to improve performance during routine surgical procedures. There is substantial, robust, international evidence that use of the WHO Surgical Safety Checklist reduces mortality and complications associated with general surgery.^11^ A checklist designed to minimise bloodstream infections associated with the routine insertion of central venous catheters in the intensive care unit is also associated with improved performance during routine healthcare delivery.^12–14^

### Checklists for healthcare emergencies

Stress affects attention and information retrieval from memory,^15 16^ and hence checklists may play a particular role in improving performance during stressful emergencies.^1 4^ Due to the unexpected, low-frequency nature of medical emergencies, crisis checklists have mainly been studied using simulation. One study reported a reduction in the frequency of unperformed lifesaving processes of care from 23% to 6% associated with checklist access during simulated surgical crises.^17^ Another study reported that checklist use increased the number of key items performed during scenarios in a simulated intensive care unit from 7 to 9.^18^ An additional study performed in a simulated surgical ward reported that use of a cognitive aid reduced the frequency of omitted critical management steps from 33% to 10%.^19^

Two studies evaluated crisis checklists in a simulated resuscitation room (RR). One study evaluated the use of an Emergency Protocols Handbook through four scenarios and reported that checklist use decreased error rate from 39% to 19%.^20^ The other study evaluated a collection of four checklists through four scenarios; checklist use was associated with an increased frequency of haemodynamic stabilisation and diagnosis recognition, as well as an increased adherence to critical steps (56% without checklist, 82% with checklists).^21^

A simulation-based, randomised controlled trial of medical crisis checklists was performed in four RRs using actual resuscitation teams during their clinical shifts.^22^ Eight medical crises were simulated. With checklist access, the median percentage of key interventions performed was 86%; without access, the median percentage was 39%.

Evidence that collections of crisis checklists and cognitive aid elements such as medication doses—emergency manuals (EMs)—improve actual clinical care is limited. Several reports document successful management of perioperative crises thanks to the use of operating room EMs.^23–26^ An interview-based study of anaesthesiologists involved in perioperative crises in 69 patients revealed that EM use led to identifying and addressing errors of omission in 59% of cases, while lack of EM use was associated with self-identified errors of omission or delays in intervention performance in 56% of cases.^5^ There is also a lack of prospective studies of EM use. One recently published prospective study reported sustained use in the operative setting multiple years after initial implementation.^27^

### Systematic crisis checklist evaluation in the clinical setting

Performance is the end-product of complex interactions between people, the tools at their disposal, and the physical and cultural environments they work in.^28^ Checklists do not work in isolation, and their impact on performance is contingent not only on their content and design but also on when, where, how and by whom they are used. Simulation-based trials and interview-based studies^29^ provide limited evidence for how checklists may actually impact resuscitation team performance in a specific clinical setting. Several authors have called for pilot studies that systematically evaluate crisis checklists in the clinical setting.^5 19 20 22 29 30^

Experts emphasise the importance of establishing the rationale for EM use, fostering a sense of local EM ownership, ensuring access and familiarity with the tool, and customisation.^31^ In particular, an explicit protocol is likely required to ensure that checklists are used as intended. A simulation-based study reported that the mere access to crisis checklists did not ensure their systematic use; only when an assigned team member read aloud the steps on the checklist were all critical actions performed.^32^ The Surgical Safety Checklist Implementation Manual emphasises the importance of clearly assigning the role of checklist implementation to a specific person^33^ and an interview-based study of EM use during perioperative crises reported beneficial effects of a reader–leader combination.^5^

Challenges to implementation and evaluation of an EM in the emergency department (ED) include the following:

The number of possible presenting complaints, acute conditions and pre-existing comorbidities among priority 1 patients is large, and the degree of actual acuity is variable.The number of personnel that work in the RR is large, and each personnel has variable context-specific degrees of expertise; managing a patient with acute pulmonary oedema may be ‘routine’ for a seasoned physician and an ‘emergency’ for a junior resident.Do-Confirm mode of checklist use is best suited to quantify the added value of checklist use, while Read-Do and Sampling modes may be best suited for checklist use during an actual crisis.Ensuring that checklists relevant to the clinical context are made available to all team members at a suitable juncture during patient management, and encouraging checklist use without negatively impacting on team dynamics, are not self-evident tasks.

These challenges have informed the study design.

### Objectives

The primary objective of the study is to determine whether Do-Confirm EM use leads to the performance, by resuscitation teams managing priority 1 patients in the ED, of additional interventions that are deemed indicated, of neutral relevance or not indicated given the clinical context. Secondary study objectives are

Determining the frequency and modality (Do-Confirm, Read-Do, Sampling) with which the EM is used and whether these changed significantly over the study period.Determining whether Do-Confirm EM use in selected cases where other modes were used might have led to the performance of additional indicated interventions.Determining the degree to which resuscitation teams find the EM helpful, and under which circumstances.

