## Methods and analysis

### Setting, patient population and personnel

The study will be carried out in the resuscitation room of the ED of Skåne’s University Hospital at Lund (referred to hereafter as Lund’s RR). Lund’s RR is designed for the simultaneous management of three priority 1 patients. EM access during clinical practice will be provided in September 2023. The study population consists of consecutive priority 1 patients managed in the Lund’s RR during the 6-month period prior to, and the 6-month pilot study period following EM implementation. Patients are deemed to be priority 1 based on vital signs and symptoms according to the Rapid Emergency Triage and Treatment System (http://predicare.se/) the most commonly used triage system in Sweden. The yearly number of priority 1 patients treated in Lund’s RR is roughly 4000 and consists of adult patients (>18 years) with medical or surgical emergencies and patients of all ages with level 1 trauma. Most of these patients are brought to the RR via ambulance, and only occasionally are they identified at the triage or at later stage of ED care. All priority 1 patients are managed immediately in the RR by multidisciplinary resuscitation teams. The core resuscitation team consists of a resident or specialist in emergency medicine, two nurses and one nursing assistant. When the patient is especially critical (for instance, cardiac arrest, level 1 trauma, upper airway obstruction), additional personnel (anaesthesiologists, surgeons, cardiologists, otorhinolaryngologists) supplement the resuscitation team.

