### Data analysis

Descriptive statistics are used to analyse EM use data and determine the following (average over and trends throughout the pilot study period):

Frequency of EM use and mode of use (Do-Confirm, Read-Do or Sampling)Which checklists or fact sheets are most frequently accessedTime between login to and logout from the digital EMSubjective degree of EM value and correlation with specific checklists or fact sheets

Descriptive statistics are also used to determine whether EM use is associated with length of stay in the RR, length of hospital admission and mortality. These analyses are hypothesis-generating and not intended to infer causality. For the 150 patients that are externally reviewed, descriptive statistics are used to report the proportions of interventions deemed indicated, of neutral value or not indicated.

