## Strengths, limitations and significance

The literature on medical crisis checklists argues that specific checklists, used according to clear protocols within specific contexts, improve performance. Yet there are no published data on how the introduction of an EM affects the performance of resuscitation teams during the management of actual priority 1 patients in the ED. The main strength of this study is that it evaluates EM use during the management of consecutive, unselected priority 1 patients by resuscitation teams in the ED.

In this study, some of the data on patient characteristics (such as age, chief complaint) and EM use (duration of use, checklists and fact sheets displayed) are automatically registered. Other EM use data (for instance, subjective team evaluation of the EM value, modality of EM use) are actively registered by the documenting nurse. The study is not a randomised controlled trial of EM use, and whether the EM is used or not is at the discretion of each resuscitation team. While these study aspects limit the evaluation of how routine EM use would impact on performance, the study will provide information about the circumstances under which resuscitation teams voluntarily use the EM and deem that it adds value to clinical practice. The study stretches over a 6-month period, allowing for an analysis of how resuscitation teams integrate a new tool within their clinical practice over time.

The study is not powered nor designed to detect causal relationship between EM use and patient outcome. The study will determine whether interventions carried out thanks to checklist use are indicated, of neutral relevance or not indicated based on the clinical context, as assessed by external reviewers. A limitation of this assessment stems from the fact that the external review is based on information available from patient records, which may not convey all the relevant factors affecting clinical decisions.

This study will be conducted in a single academic Swedish ED, limiting the external validity of the results. Yet this study will provide valuable information to guide the development of a tool that has the potential to improve the management of critical patients, and pave the way to multicentre studies of EM use in the ED.

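### The first secondary objective asks whether use and mode of the emergency manual changed significantly, but the named analysis is descriptive and gives no basis for judging change

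*Protocol article*

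**What the plan says.** The Objectives section of the protocol article lists as its first secondary objective: "Determining the frequency and modality (Do-Confirm, Read-Do, Sampling) with which the EM is used and whether these changed significantly over the study period". The part at issue is the last clause, "whether these changed significantly over the study period".

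The Data analysis section names the method for EM use: "Descriptive statistics are used to analyse EM use data and determine the following (average over and trends throughout the pilot study period". The first item under that sentence is "Frequency of EM use and mode of use (Do-Confirm, Read-Do or Sampling", the same pair of quantities as in the objective.

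The rest of that section is descriptive as well. On patient outcomes it says: "Descriptive statistics are also used to determine whether EM use is associated with length of stay in the RR, length of hospital admission and mortality". For the externally reviewed cases, "descriptive statistics are used to report the proportions of interventions deemed indicated, of neutral value or not indicated".

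The closing section on strengths and limitations returns to change over time and says of the six-month period that it is "allowing for an analysis of how resuscitation teams integrate a new tool within their clinical practice over time".

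**The concern.** The objective asks an inferential question: is the change in use or mode larger than chance variation would explain? The analysis named for it yields averages and a trend line, and nothing says how large or how certain a change must be to count as significant.

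The practical risk is in the reporting. Whoever writes the results must either leave the word in the objective unanswered, or choose the time unit, cut-points and test after seeing the curve. A later statement that use significantly rose or fell would then rest on choices made after the fact, or would carry no measure of uncertainty.

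**Working it through.** **Step 1. Compare the texts.**

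| | Objectives | Data analysis |
|---|---|---|
| Quantity | Frequency and mode of EM use | Frequency and mode of EM use |
| Question | Level, and significant change over the period | Average, and trend over the period |
| Method | Not stated there | Descriptive statistics |
| Interval, test or criterion | Implied by the word significantly | None stated |

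The level and the observed trend match. The significance of the change does not.

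**Step 2. Look for a test elsewhere.** The only hypothesis test is in the Sample size calculation section. It concerns the proportion of interventions graded as indicated: null at most 10%, alternative 21%, 75 interventions, at least 80% power, α at most 0.05. That figure reproduces. An exact one-sided binomial test with n = 75 rejects at 13 or more indicated interventions, with α = 0.034 and power 82.1%. It has no bearing on change over time, and the article gives no figure for change over time.

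**Step 3. Could the data carry a test of change?** The Setting section gives the volume: "The yearly number of priority 1 patients treated in Lund’s RR is roughly 4000". Six months therefore give 4000 / 2 = 2000 patients, or 1000 in each half. The article gives no expected use rate, so the rates below are assumptions.

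Two proportions, n = 1000 per half, two-sided 5%, with p̄ the mean of the two rates:

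- SE = √(p̄(1 − p̄) × 2/n), z = difference / SE, power ≈ Φ(z − 1.96).
- 40% against 34%: p̄ = 0.37, SE = √(0.37 × 0.63 × 2/1000) = 0.0216, z = 0.06/0.0216 = 2.78, power = Φ(0.82) = 79%.

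For a 5-point rise under independence, across assumed first-half rates:

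| First-half rate | 10% | 20% | 30% | 50% |
|---|---|---|---|---|
| Power | 92% | 76% | 67% | 61% |

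**Step 4. Allow for clustering.** Use depends on the nurse and team on duty, so patients are unlikely to be independent. A design effect D multiplies the SE by √D and divides z by √D. The values of D are assumptions.

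- 40% against 34%, D = 1.5: z = 2.78/1.225 = 2.27, power about 62%.
- 40% against 34%, D = 2: z = 2.78/1.414 = 1.97, power about 50%.
- 40% against 30%: p̄ = 0.35, SE = 0.0213, z = 4.69. At D = 2, z = 3.32 and power is about 91%. At D = 3, z = 2.71 and power is about 77%.

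A change of about 10 points from 40% is thus testable under fairly heavy clustering, while a change of about 6 points may not be. No comparable figure can be given for mode, because the number of EM-use episodes is unknown.

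**The case against.** The strongest reply is that this is one word against one label. The analysis section does not say that only descriptive statistics will be used, and it excludes neither intervals nor tests. It uses the term loosely, applying it also to correlations and associations, so the word significantly in the objective may be equally loose. The article is condensed, and a trend model for a secondary objective is commonly left to an analysis plan, which is not shown here.

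Much of this stands, and it rules out several stronger readings that a reader might infer:

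- That the objective cannot be answered at all. Frequency, mode and their trends are covered.
- That any statement of rising or falling use would be unsupported. The patients are consecutive and activation is recorded automatically, so a change within this department would be observed directly. Inference bears on whether it exceeds chance variation.
- That six months were chosen in order to study uptake. The article says that the period allows such an analysis, and does not give this as the reason for the length.

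What does not stand is the appeal to an unseen plan as a complete answer. The article is not silent here: it names a method for this exact item, and that method does not fit the objective. An analysis plan that followed the article would leave the significance question open, and one that added a test would go beyond the method the article names. The two sections still need to be aligned.

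**Conclusion.** The mismatch is real but narrow. Of the first secondary objective, only the part about significant change has no matching analysis. This follows from the text and rests on no assumption about rates.

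The power figures show only that a test would be worth specifying. They depend on assumed use rates, an even split of about 2000 patients and an assumed degree of clustering. The 79% for a 6-point fall is a favourable case, and about 50% at a design effect of 2 is equally plausible on what the article gives.

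Severity is minor. The objective is secondary, the data needed are already being collected, and the primary outcome does not depend on it.

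**What to change.** In the Data analysis section, add a trend analysis for this objective.

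- **Frequency.** For each calendar week, count the priority 1 patients and the EM-use episodes among them. Count log-ins with actual use and leave out log-ins recorded as non-use, since the protocol for use separates the two. Regress the weekly proportion on calendar time with a quasi-binomial or other overdispersion-robust model, and report the odds ratio per month with its 95% confidence interval. Grouped weekly counts are needed because dispersion cannot be estimated from single yes/no records. Clustering on the nurse is not available here, because the nurse's identification is recorded only when the EM is activated.
- **Mode.** Among EM-use episodes, fit a separate logistic model for each mode (used or not used in the episode) on calendar time, with standard errors clustered on the logged-in nurse and 95% confidence intervals. Separate models are preferable to one multinomial model because the default mode differs by type of checklist, so one episode may contain several modes.

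The alternative is to reword the objective so that it sets out to describe trends.

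The cost is a change of wording and a few hours of analysis, with no new data. The drawback is that precision depends on the use rate and the clustering, both unknown, so the intervals may be wide.
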